#### Intramuscular adaptations

Vastus lateralis muscle biopsies are sampled in Umeå (10–16 pre/post biopsies) and in Quebec (10–16 pre/post biopsies) to assess muscle fiber size, expression of slow and fast subtypes of contractile myosin heavy chain isoforms in fibers, oxidative (CS, EC 4.1.3.7) and glycolytic (LDH, EC 1.1.1.27) enzyme activities as well as capillarization (capillary density, number of capillaries around fiber and capillaries around fibers relative to its cross-sectional area).

Possible correlations between capillary parameters, fiber phenotype composition, fiber cross-sectional area, enzymatic activity and other outcome measures, such as quadriceps muscle strength and endurance, after the resistance training interventions will be evaluated.

### Data management

All data will be coded and reported on a group level. It will not be possible to identify specific individuals in the trial. The participants’ identities will only be known by the research group at respective center and the principal investigator.

The REDCap (Research Electronic Data Capture) Survey, a secure, Health Insurance Portability and Accountability Act compliant, web-based survey application will be used to manage and store project data [49]. To ensure confidentiality, data dispersed to project team members will be blinded of any identifying participant information. All records that contain names or other personal identifiers, such as locator forms and informed consent forms, will be stored separately from study records identified by code number at local research centers, respectively. All local databases will be secured with password-protected access systems.

### Statistics

The primary analyses will be an intention-to-treat analysis (including all participants randomized) in addition, a complete case population (participants with complete outcome measurements independent on adherence to intervention), and a per-protocol analysis (defined as at least 80% overall attendance rate as well as no exacerbations during the last 2 weeks prior to follow-up assessment) will be performed. Missing data will be imputed in the intention-to-treat analysis using multiple imputation assuming data is missing at random conditional on participant severity of disease and history of exacerbations. This is because severity of disease and history of exacerbations are known risk factors for future exacerbations and may affect adherence to the training protocol [28].

Mixed models will be used for analysis of data with individuals at level 1 and center at level 2. Estimates of effect sizes will be computed using Cohen’s *d* (*d* = difference in group means/error SD within). Calculated as the difference between predicted means from the final mixed-effects model for a given pair of groups divided by the estimated within-group error SD in the model with the estimated value of $$ 2{\sigma}_e^2 $$, where $$ {\sigma}_e^2 $$ is the residual variance. To judge the quality of the model we will analyze the residuals. For responsiveness, values of 0.20, 0.50 and ≥ 0.80 correspond to small, moderate and large responsiveness, respectively [50].

We will consider two-sided *p* values < 0.05 as statistically significant for the primary outcomes without correction for a multiplicity of tests assuming that each test represents an independent function based on the specificity principle of training [26]. Relationships between parameters will be evaluated using Pearson correlation coefficients. The strength of the correlation coefficients will be categorized as low (0–0.25), moderate (> 0.25–0.50), strong (> 0.50–0.75), very strong (> 0.75). Pre-planned subgroup analyses are differences between men and women. Statistical analysis will be performed using the statistical package SPSS 23.1.

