### Primary objective

To compare the effect of NLPRT with RT on isotonic upper (chest press, shoulder flexion) and lower (leg press, calf press) limb-muscle strength and limb-muscle endurance in people with COPD.*Hypothesis*: NLPRT will result in a similar effect size with regard to isotonic leg press, chest press, calf press and shoulder flexion muscle strength but in a larger effect size (> 1.16) with regard to muscle endurance than traditional RT at week 9

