### Sample size calculation

Multicenter trials involve a correlation in data, i.e., participants from the same center are likely to be more similar than subjects from other centers. As such, a correlation potentially affects the statistical power of the trial the sample size needs to be adjusted, often increased, to account for the design of the study [21]. To minimize the effect of using different centers, eligibility criteria as well as design and delivery of training interventions are standardized across centers. Furthermore, in an individually randomized trial that is stratified for centers, similar to the present trial, the design effect is estimated to be < 1 which involves a gain in power, allowing a reduction in sample size rather than an increase [21, 22]. Nevertheless, the sample size calculation is performed with a design effect of 1 and is based on the results from a resistance training meta-analysis on healthy adults in which a group difference of 1.16 (SD 1.09) was seen on muscle function when comparing NLPRT with RT [18]. Thus, based on an expected group difference in effect size of 1.16 (SD 1.09) on muscle function with a power of 80%, two-sided alpha of 0.05 (including 15% drop-outs) 16 patients per group is required (32 in total). However, we plan to recruit a total of 64 patients with an equal distribution of men and women. The planned sample size (*n* = 64, including 15% drop-out) will be sufficient to have power for subgroup analysis based on sex (male and female).

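### The Cohen's d denominator is named a within-group error SD but given the value of twice the residual variance, so the scale of the reported effect sizes is undefined

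*Protocol article*

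**What the plan says.** All of the wording on how d is computed is in the Statistics section of the protocol article.

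- The model: "Mixed models will be used for analysis of data with individuals at level 1 and center at level 2". No occasion level and no participant effect is mentioned.
- The definition of d in words: "difference in group means/error SD within".
- The computation: the difference between predicted means is "divided by the estimated within-group error SD in the model with the estimated value of" 2σ_e². The formula carries no root sign, and the text explains that σ_e² "is the residual variance".

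The effect-size scale is also used elsewhere. Under Primary objective, the hypothesis expects a similar effect size for strength, "but in a larger effect size (> 1.16) with regard to muscle endurance than traditional RT at week 9". The Sample size calculation section plans on an "expected group difference in effect size of 1.16 (SD 1.09) on muscle function". No section restates or corrects the denominator.

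**The concern.** The words and the formula give different denominators. The words call for a standard deviation, in the units of the outcome. The formula gives a variance, in squared units, and doubles it. Both cannot be applied.

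This matters because effect size is more than a descriptive extra here: the primary endurance hypothesis is written as a threshold on it. Whether an observed d exceeds 1.16 depends on the denominator. If that choice is left until the data are in, it could decide the answer. The primary outcomes are also measured in different units, loads for 1RM and counts for endurance, so a d that is not unit-free could not be compared between strength and endurance, as the hypothesis does.

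**Working it through.** **Inputs.** Benchmark 1.16 (Primary objective); planning values 1.16 and SD 1.09, "with a power of 80%, two-sided alpha of 0.05", 15% drop-out, 16 per group (Sample size calculation); denominator 2σ_e² and two-level model (Statistics). The documents give no residual SD in kilograms or repetitions and no pre-post correlation, so values of these are assumptions, shown over a range.

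**Step 1. The plan's own figure.** Normal approximation: n = 2 × (1.960 + 0.842)² × (1.09/1.16)² = 13.9, so 14 per group; 14/0.85 = 16.5, so 17. A t-test calculation with d = 1.16/1.09 = 1.064 gives 15, then 18 after drop-out. A t-test calculation with d = 1.16 (SD 1) gives 13, then 16. The stated 16 is reproduced within two patients, and none of these calculations uses the 2σ_e² formula.

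**Step 2. The formula taken literally.** Let the true difference be 1.16 × σ_e. Then d = 1.16σ_e/(2σ_e²) = 0.58/σ_e.

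| Assumed σ_e | d with σ_e | d with √(2σ_e²) | d with 2σ_e² |
|---|---|---|---|
| 0.25 | 1.16 | 0.82 | 2.32 |
| 0.5 | 1.16 | 0.82 | 1.16 |
| 1 | 1.16 | 0.82 | 0.58 |
| 5 | 1.16 | 0.82 | 0.116 |
| 10 | 1.16 | 0.82 | 0.058 |
| 20 | 1.16 | 0.82 | 0.029 |

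The literal formula agrees with d on σ_e only when σ_e = 0.5. Unit check: a difference of 11.6 kg with σ_e = 10 kg gives 11.6/(2 × 100) = 0.058. In pounds (factor 2.20462) the same data give 0.058/2.20462 = 0.026. With σ_e = 10 repetitions, reaching 1.16 would need a difference of 1.16 × 2 × 100 = 232 repetitions, against 11.6 when dividing by σ_e.

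**Step 3. A square root was dropped, with the two-level model.** With individuals within centers and one residual per person, the within-group error SD is σ_e. Dividing by √(2σ_e²) = 1.414σ_e multiplies d by 1/1.414 = 0.71. A value of 1.16 on the σ_e scale is reported as 1.16/1.414 = 0.82, and reporting 1.16 would need 1.16 × 1.414 = 1.64.

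**Step 4. A square root was dropped, with a repeated-measures model.** With two visits per person and a participant effect, σ_e² = SD²(1 − ρ), where SD is the between-participant SD at one visit and ρ is the pre-post correlation. Then √(2σ_e²) = SD × √(2(1 − ρ)), which is the SD of a change. Relative to d on the between-participant SD, d is multiplied by 1/√(2(1 − ρ)): 1.00, 1.29, 1.58 and 2.24 for assumed ρ of 0.5, 0.7, 0.8 and 0.9.

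Steps 3 and 4 each give a legitimate SD of something, but with different multipliers, and only Step 3 corresponds to the model that the section describes.

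**The case against.** The strongest reply is that this is a typographical slip. The denominator is twice called an SD in words, a missing square root is plausible, and nobody is likely to divide by a variance in practice. That stands as an account of how the error probably arose. It does not settle the matter, because restoring the root gives the wrong SD for the stated model (Step 3).

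A second reply is that one residual per person is an inference. The section does not say whether the outcome is the week 9 value, the change or both visits; the design is pre-post, and the printed factor of 2 may itself point to a repeated-measures model. Model terms are also commonly left to a fuller document. This stands in part: it means that the direction of the distortion cannot be fixed from the article. It does not rescue the formula, since that model would have to be stated.

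A reader might infer more than the documents support, in four ways:

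- That the sample size or the tests are compromised. Significance is judged by two-sided p < 0.05 from the models, which does not use d, and the sample size does not use this formula.
- That d will be off scale against the meta-analysis behind 1.16. The article does not say which standardizer that figure used, so comparability is unknown either way.
- That the baseline SD should be the denominator. It is one choice among several and doubtful for endurance: the upper limit of 60 repetitions is stated for baseline testing, with a retest at higher resistance, and could compress the baseline SD and inflate d. Equipment also differs between centers, so an SD pooled only within arm would absorb differences that the center level removes.
- That covariate adjustment for baseline shrinks σ_e further. The article mentions no such covariate.

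**Conclusion.** The point holds as an error in a stated formula. The denominator is described as an SD and given the value of a doubled variance, and nothing in the article corrects it. Literally, d equals 0.58/σ_e for a true difference of 1.16σ_e and so changes with the units. With a root restored and the two-level model read as one residual per person, d is 0.71 of its value on σ_e (0.82 for 1.16). With a root restored and a repeated-measures model, d is on the change-score scale, 1.29 to 2.24 times the between-participant value for assumed correlations of 0.7 to 0.9.

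The consequence is confined to the reported effect sizes and to the reading of the endurance hypothesis against 1.16. It should be corrected before analysis, but it does not threaten the primary tests or the planned number of patients.

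**What to change.** Replace 2σ_e² with a single SD that is dimensionally valid, matches the stated model and is fixed before the data are analysed:

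- If the two-level model stands, use σ_e, the square root of the residual variance.
- If a repeated-measures model is intended, state it with its participant effect, use √(2σ_e²), and label d as change-score scaled.

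Report each d with a 95% CI, beside the between-group difference in original units. It would also help to say which standardizer the 1.16 threshold is taken to refer to, or that this is not known.

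The cost is one corrected formula and a sentence or two. No patients, measurements or trial procedures change, and the Amendments section already provides for clarifications of this kind.

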### Secondary objectives

2.To compare the effect of NLPRT and RT on (1) functional performance measured with the endurance shuttle walk test (ESWT), the 60-s Sit to Stand Test (60STS) and the Unsupported Upper Limb Exercise Test (UULEX), (2) isometric quadriceps muscle strength and endurance, (3) health-related, disease-specific quality of life (HRQoL), (4) dyspnea and (5) the proportion of responders for each of these variables (a response being defined as an improvement that is larger than the known minimal detectable change/or minimal important difference for a given variable).*Hypothesis*: NLPRT will result in a greater gain on functional performance, isometric quadriceps muscle endurance, HRQoL dyspnea, as well as a larger number of responders while effects will be similar with regard to isometric muscle strength at week 93.To determine the feasibility of NLPRT compared to RT on attendance rate, duration, satisfaction, drop-outs as well as occurrence and severity of any adverse events.*Hypothesis*: that NLPRT will be feasible to the same extent as RT over 8 weeks of training4.To determine the responsiveness of isometric quadriceps strength and endurance measurement to NLPRT and RT.*Hypothesis*: isometric quadriceps muscle strength measurements will be highly responsive to NLPRT as well as RT represented by a standardized response mean (SRM) > 0.80, while quadriceps endurance measurements will be highly responsive to NLPRT but moderately responsive to RT (SRM 0.50 > 0.80) at week 95.To explore the intramuscular adaptations of NLPRT compared to the intramuscular adaptations of RT*Hypothesis*: NLPRT will result in a larger increase in muscle capillarization as well as in the activity of citrate synthase (CS) and lactate dehydrogenase (LDH) compared to RT at week 9

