### Randomization and masking

A person not involved with either enrollment, assessments nor training of participants will generate the allocation sequence and assign participants to one of the two interventions.

To prevent foreknowledge of treatment assignment and to keep the allocation sequence concealed from the participants and the researchers, group allocation will be done after the completion of baseline and inclusion tests with a computer random-number generator. Individual randomization, stratified for centers and sex, will be performed with a 1:1 allocation to the intervention and control groups. The allocation sequence will be kept in an opaque, sealed and stapled envelope and will be kept concealed until the end of the outcome assessment. The envelope will be made impermeable to intense light by using aluminum foil inside and sealed using tamper-proof labels.

The outcome assessors will be masked to group allocation. Furthermore, the participants will be given repeated instructions not to reveal their group allocation to the outcome assessors. In case of failure in keeping the outcome assessor masked (i.e., a patient reveals their group allocation), a second trained outcome assessor will be available.

Due to the nature of the intervention neither participants nor instructors of the training sessions will be masked during the intervention, the hypotheses of the trial will, however, not be revealed to the participants before and during the trial. The data analysts will be masked to group allocation.

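### Unadjusted Pearson correlations between biopsy and function measures can reflect arm, sex or center differences rather than an association within those groups

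*Protocol article*

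**What the plan says.** Under Intramuscular adaptations, the protocol article plans to examine "Possible correlations between capillary parameters, fiber phenotype composition, fiber cross-sectional area, enzymatic activity and other outcome measures". It gives the quadriceps measures as examples of those outcomes and places the assessment at the end of training. The material comes from two of the four centers: "Vastus lateralis muscle biopsies are sampled in Umeå (10–16 pre/post biopsies) and in Quebec (10–16 pre/post biopsies", which makes 20 to 32 patients. The Statistics section names the method in one sentence, "Relationships between parameters will be evaluated using Pearson correlation coefficients", and adds the labels: "The strength of the correlation coefficients will be categorized as low (0–0.25), moderate (> 0.25–0.50), strong (> 0.50–0.75), very strong (> 0.75"). No covariate, stratum or arm-specific coefficient is mentioned for these correlations, and it is not said whether week 9 values or changes from baseline are correlated.

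Four other statements bear on this:
- Objective 5 under Secondary objectives expects that "NLPRT will result in a larger increase in muscle capillarization", and likewise larger increases in citrate synthase and lactate dehydrogenase activity. The hypothesis for objective 2 expects a greater gain in isometric quadriceps endurance with NLPRT, but similar isometric strength in the two arms.
- Sample size calculation says that "participants from the same center are likely to be more similar than subjects from other centers".
- Randomization and masking: "Individual randomization, stratified for centers and sex, will be performed with a 1:1 allocation to the intervention and control groups".
- Isometric quadriceps strength and endurance allows the measuring device to depend on what each center has.

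The outcome analysis places center at level 2 of a mixed model. Nothing equivalent is stated for the correlations.

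**The concern.** The question is whether patients with more muscle adaptation also have better function. An unadjusted Pearson coefficient answers it only if the sample is homogeneous. Here the sample mixes arms, centers and, in all likelihood, sexes. Any factor that moves both variables in the same direction creates a positive pooled correlation even if the two are unrelated inside every group. Shifts in opposite directions create a negative one. A factor that moves only one variable dilutes a real link.

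The arm is the clearest case, because the protocol itself predicts that NLPRT shifts both the biopsy measures and quadriceps endurance. If both predictions come true, a pooled coefficient between them partly restates the treatment effect and could be read as evidence that individual muscle adaptation tracks individual function. The strength labels would carry the same distortion.

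**Working it through.** **The plan's own figure.** No power or sample size is given for the correlations. The only effect size with an SD in the document is in Sample size calculation: 1.16 (SD 1.09), 80% power, two-sided 0.05, 15% drop-out. The normal approximation gives 2 × [1.09 × (1.96 + 0.84)/1.16]² ≈ 13.9 per group, and 13.9/0.85 ≈ 16.3, consistent with the stated 16. The plan therefore works with a standardized difference of 1.16/1.09 = 1.06. I borrow it below as an assumption. It comes from healthy adults and general muscle function, and the document gives no size for the arm difference in the biopsy measures or in isometric endurance.

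**Expected pooled correlation.** Take two equal groups, no association within either, and mean differences of dx and dy in within-group SDs:

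r = (dx·dy/4) / √[(1 + dx²/4)(1 + dy²/4)]

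With the same d in both variables this is (d²/4)/(1 + d²/4):
- d = 0.5: 0.0625/1.0625 = 0.06
- d = 1.0: 0.25/1.25 = 0.20
- d = 1.06: 0.283/1.283 = 0.22
- d = 1.16 (reading the planning figure as already standardized): 0.336/1.336 = 0.25
- The expected r reaches the moderate boundary of 0.25 at d = 2√(0.25/0.75) = 1.15.

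For several balanced factors the d²/4 terms add. With arm, sex and center at 0.8 SD each, 3 × 0.16 = 0.48 and r = 0.48/1.48 = 0.32. If the biopsy measure shifts less than endurance, say 0.5 against 1.06, r = 0.11.

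**Masking.** A difference of 1.06 SD in opposite directions gives r = −0.22. If a factor shifts only one variable by d, a true within-group r of 0.5 becomes 0.5/√(1 + d²/4), which is 0.35 at d = 2.

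**Simulation** (40,000 runs per setting; arm, sex and center balanced or nearly so; within-group association zero). The adjusted coefficient is the partial correlation given arm, sex and center. The significance column uses a nominal 5% test for reference only, because the document does not attach one to these correlations.

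| Assumed shift, both variables | n | Mean pooled r | Pooled \|r\| > 0.25 | Pooled p < 0.05 | Adjusted \|r\| > 0.25 | Adjusted p < 0.05 |
|---|---|---|---|---|---|---|
| None | 20 | 0.00 | 29% | 5% | 33% | 5% |
| None | 32 | 0.00 | 17% | 5% | 19% | 5% |
| Arm 0.5 | 20 | 0.06 | 31% | 6% | 34% | 5% |
| Arm 0.5 | 32 | 0.06 | 19% | 6% | 19% | 5% |
| Arm 1.06 | 20 | 0.23 | 50% | 16% | 33% | 5% |
| Arm 1.06 | 32 | 0.22 | 46% | 24% | 19% | 5% |
| Arm, sex, center 0.8 each | 20 | 0.33 | 69% | 30% | 33% | 5% |
| Arm, sex, center 0.8 each | 32 | 0.33 | 71% | 47% | 19% | 5% |

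Counting only positive values, r > 0.25 occurs in about 45% of runs at n = 32 with the arm shift of 1.06, against about 8% with no shift. Adjustment removes the bias in every setting but not the chance excess over 0.25.

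**Which shifts are plausible depends on what is correlated.** If week 9 values are used, stable differences between the sexes in strength and fiber size, and between centers in device, enter in full. If changes are used, those level differences largely cancel and mainly the arm difference remains.

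**The case against.** Much of the case on the other side stands.

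- A reader might infer that the plan commits to pooling. It does not say so, and coefficients within each arm are not excluded. Pooling is only the natural reading: one coefficient is named, and within-arm samples would be about 10 to 16. A journal article may leave such detail to a fuller document.
- A reader might infer that false-positive findings are built in. The 0.05 threshold is stated for the primary outcomes only. For the correlations, only descriptive labels are planned.
- A reader might infer that group differences by themselves will produce moderate correlations. They can, but at 0.5 SD in one factor the expected r is 0.06.
- Equal numbers of men and women are planned for all 64 recruits. Biopsy is optional, and no sex mix is given for that subset, so the balance in the simulation is assumed.
- Nearly all the shifts are assumed. For strength, the protocol predicts similar arms, so arm confounding of the strength correlations is not expected. The document does not say that the two biopsy centers use different devices.
- Adjusting for arm is a choice of question: it removes the variation created by the difference between the programs.

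The objection does not remove the point that the one method named cannot separate an association within groups from shared group differences, while the protocol predicts such a difference in both biopsy measures and endurance. Naming a better method is therefore more than a request for detail.

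**Conclusion.** The point holds as a minor improvement to an exploratory analysis. If arms, sexes and centers are pooled, as the text most naturally reads, the unadjusted coefficient can be inflated or masked by group differences. With an arm difference of 1.06 SD in both variables and no within-group association, the expected r is about 0.22. At 0.5 SD the distortion is negligible. The arm effect matters for endurance, not for strength on the protocol's own hypotheses. Sex and center differences matter mainly if week 9 values rather than changes are correlated.

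These sizes rest on assumed shifts and balanced groups. It would go too far to conclude that the biopsy correlations are bound to mislead, or that any primary conclusion is affected. The objective is exploratory and the primary outcomes are analyzed separately.

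**What to change.** In the Statistics section, replace the sentence on Pearson coefficients, for the biopsy–function relationships, with:
- the week 0 to week 9 change in the biopsy measure related to the change in the functional outcome;
- a partial correlation or linear model adjusted for arm, sex and center;
- a 95% confidence interval and a scatter plot with the arms marked;
- any strength label based on the adjusted coefficient only, with a note that labels are unreliable at 20 to 32 patients. For an adjusted r of 0.25, the Fisher interval tanh[atanh(0.25) ± 1.96/√(n − 6)] runs from −0.13 to 0.56 at n = 32 and from −0.26 to 0.65 at n = 20.

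All three factors are known by design, so nothing new is collected. The cost is three degrees of freedom. By simulation with a true r of 0.5 and no group shifts, power falls from about 85% to 82% at n = 32 and from about 64% to 56% at n = 20.
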